# Methods

1. Intervention

〇Active

・GBE/MST capsule (commercially known as “Brain assist ®︎”)

Ginkgo biloba extract, sesame oil, Piper longum extract, reduced sugar syrup, refined fish oil containing docosahexaenoic acid with gelatin, spice extract, glycerin, glycerin fatty acid ester, beeswax, caramel color, vegetable lecithin from soybean

4 kcal, proteins: 0.2g, lipids: 0.3g, carbohydrates: 0.2g, salt: 0.0008g

・GBE capsule (commercially known as “Icho-ba Ekisu”)

Ginkgo biloba extract, reduced sugar syrup, gelatin, glycerin fatty acid ester, caramel color, tocotrienol lecithin from soybean

5 kcal, proteins: 0.2g, lipids: 0.4g, carbohydrates: 0.2g, salt: 0.0009g

Both have a dosage of two capsules per day. Both the products will be provided by Ohki Pharmaceutical Company and will have similar shapes, colors, and tastes. The package containing the products will not have any information to avoid participant bias.

〇Placebo

Placebo will be made in matched for size, color and taste to the GBE/MST capsule and GBE capsule.

Reduced sugar syrup, refined fish oil containing docosahexaenoic acid with gelatin, spice extract, glycerin, glycerin fatty acid ester, beeswax, caramel color, vegetable lecithin from soybean

5 kcal, proteins: 0.2g, lipids: 0.5g, carbohydrates: 0.1g, salt: 0.0009g

1. **Dosage and administration**

Participants in the GBE/MST group will consume two capsules of the GBE/MST supplement. Participants in the GBE group will consume two capsules of GBE supplement. Participants in the placebo group will consume two capsules of placebo.

1. **Adverse effects and cessation criteria**

The adverse effects will be screened throughout the study period. Headache, dizziness, tinnitus, diarrhea, nausea, gastrointestinal symptoms, high blood pressure, excessive thirst, dyspnea, chest pain, bradycardia, and upper respiratory infection have been reported as adverse effects of GBE [5]. Interestingly, participants consuming GBE showed a lower incidence of adverse events when compared with those consuming a placebo [10]. The study will be terminated if any grade 3 adverse event is reported. If a participant shows any adverse events and requests a refusal, the study will be terminated.

1. **Schedule**

At registration, written informed consent will be obtained from the participants. Subsequently, cognitive function will be evaluated using the MoCA-J. Participants with a score of ≧26 will be eligible for inclusion.

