・Inform that the examination can stop anytime during the procedure if a participant will feel any abnormalities.

2. Since the MRI apparatus has strong magnetic field, metallic materials can be pulled and may physically injure a participant. Counterplans are described below:

・Metallic material without anchoring must not be stored in the MRI room.

・The exclusinve stuffs of MRI must control the procedures in the MRI room which has protective methods against expecting risks.

3. There is a possibility of finding any critical diseases, such as brain tumore, brain absess, brain hemorrhage, brain infarction, brain artery aneurysm, arteriovenous malformation, etc., by analysis of MRI. If any of such abnormality will be found, an investigator will inform the participant about to ask a doctor.

4. During MRI procedures, undesired noise, magnetic field, change of body temperature, and unconfortable position in narrow space may cause discomfort. As counterplan of discomfort, a participant can use a buzzer for alart any bad feeling. If a buzzer sounds, an operator must stop the procedure, and a doctor must check a participant’s condition. In case of difficultiness, the MRI procedure can be cancelled.

Risks and adverse events regarding GBE and GBE/MST

　GBE, sesame extract, and turmeric oil have been used as suppliments, and their safety has been established. No critical adverse event was reported. Digestive symptoms and thirsty have been reported as side effects. These symptoms will diminish after 3-4 days of cessation. If such side effects are strong, participation of this study can immediately be stopped.

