**^1)^ Classification of severity**

For evaluation of adverse event / incident, Japanese version of NCI-CommonTerminology Criteria for Adverse Events v4.0 (CTCAE v4.0-JCOG) is used.

About the CTCAE v4.0-JCOG items of which grade is defined as an institutional standard, “JCOG reference range” will be adopted instead of each institutional standard. Precise information about “JCOG reference range” is available in the website (http://www.jcog.jp/doctor/tool/kijun.html）.

If there is no applicable grade in the NCI CTCAE grade, decision will be performed following the **Severity classification standard for adverse events**.

| **NCI CTCAE Grade** | **Severity classification standard for adverse events** |
| --- | --- |
| **Grade1** | No or mild symptom. Only clinical or laboratorical abnormality.  No needs to treat. |
| **Grade2** | Minimal/partial/non-invasive treatment.  Restriction of instrumental ADL*, except for age-appropriate personal activity. |
| **Grade3）** | Severe or medically important, but not critical.  Need in-patient treatment or extension of hospitalization.  Incapacity / inoperability. Restriction of self care ADL**. |
| **Grade4** | Life-threatening. Need emergency treatment. |
| **Grade5** | Death caused by the adverse event. |

* instrumental ADL

：preparation for meal, daily shopping, telephone use, management of money, etc.

** self care ADL

：bathing, changing, eating, toileting, and ingestion. Not bedridden.

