# Description of adverse events

Investigators etc. must describe in the CRF about name, severity (seriousness, non-seriousness), reason of desiding seriousness, date of onset and prognosis, treatment, outcome (recovered, remission, recovered with sequera, not recovered, or death), relationship with the relevant medicine/appalatus, comments (causality and reason of decision) regarding all adverse events.

- 1. The name of adverse event must be written with diagnosis name/ disease name in the CRF. If diagnosis name/ disease name can not be specified or investigators etc. decide appropriate not to describe diagnosis name/ disease name, clinical condition or symptoms (including abnormal lab data) can be alternatively written in the CRF.
  2. Describe the treatments (yes/no) for adverse events of the participant.

③ Describe the outcome of adverse events.

| **Outcome** | **Description** |
| --- | --- |
| Recovered | The adverse event is eliminated, or it returns to original. |
| Remission | Although the adverse event is not completely recovered, it is almost eliminated or returns to almost original. |
| Recovered with sequera | Although the adverse event is returned to original, a sequera remains. |
| Not recovered | The adverse event is ongoing. |
| Death | The adverse event causes death. |

Definition of adverse events:

All undesirable or unexpected diseases and injury or symptoms (including lab data abnormality) regardless of causality to the study. Collection of adverse events will be performed from registration to the end or termination of observation of each participant.

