# Response to the serious adverse event / incidents (including adverse events to be reported to head of the research institute)

# Response to the adverse event / incident

1. In case of the adverse events / incidents, investigators etc. must deal with them appropriately. Investigators etc. must investigate their cause with extreme care of the participant.
2. Investigators etc. must continue observation and check the outcome of symptoms and lab data abnormality until they are eliminated or return to original or are diagnosed normal as long as possible.
3. If the adverse event / incident is not recovered or irreversible at the end of the study, or if investigators etc. decide it is not necessary to chase, investigators etc. can cease the observation at the end of the study and describe the reason why it is decided as no-need to chase in the comment field of the CRF.

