**Necessity and period of report to head of the research institute and principal investigator (research director)**

**Causality no**

**Causality yes**

|  | **Grade1/2/3** | | | **Grade4** | | **Grade5** | | **Others, medically important condition** |
| --- | --- | --- | --- | --- | --- | --- | --- | --- |
|  | **Predictable (Known)** | **Unpredictable (Unknown)** | | **Predictable (Known)** | **Unpredictable (Unknown)** | **Predictable (Known)** | **Unpredictable (Unknown)** |  |
|  | **hospitalization**  **yes／no** | **hospitalization**  **no** | **hospitalization**  **yes** |  |  |  |  |  |
|  | Reoprt  necessary | Reoprt  unnecessary | Initial report:  within 10d  Additional report: occasionaly | 1^st^ report: within 72h  2^nd^ report: within 7d  Additional report: occasionaly | | | |  |
|  | Reoprt  unnecessary | Reoprt  unnecessary | Initial report:  within 10d*  Additional report: occasionaly* | 1^st^ report: within 72h*  2^nd^ report: within 7d*  Additional report: occasionaly* | | | |  |

* during treatment or within 30 days from the last protocol treatment

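### The only grade-based cessation rule names grade 3 without adding higher grades, so read literally it omits life-threatening events, and it does not say who stops (minor)

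*Protocol*

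**What the plan says.** The cessation criteria are in the Methods section, under adverse effects and cessation criteria. Two sentences set them. The first is grade-based: "The study will be terminated if any grade 3 adverse event is reported". The second depends on the participant's wish: "If a participant shows any adverse events and requests a refusal, the study will be terminated".

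The section on classification of severity adopts CTCAE v4.0-JCOG and lists five grades. Grade 3 begins "Severe or medically important, but not critical". Grade 4 is a separate row: "Life-threatening. Need emergency treatment". Grade 5 is death caused by the event.

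The section on burdens and foreseeable risks adds a permissive stop for the study products: "If such side effects are strong, participation of this study can immediately be stopped". It follows a description of digestive symptoms and thirst.

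Adverse events are defined in the section describing them as "All undesirable or unexpected diseases and injury or symptoms (including lab data abnormality) regardless of causality to the study".

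**The concern.** A stopping threshold on an ordered severity scale has to name the threshold grade and everything above it. This one names a single grade. Read as written, it requires a stop for an event that the protocol's own table describes as not critical, and requires none for one that is life-threatening.

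The sentence also does not say what stops. The words could mean that participant's involvement or the whole trial. The two readings differ greatly in consequence, because adverse events are counted whether or not they are related to the study.

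What is at stake is the correctness of a mandatory safety instruction that investigators and the ethics committee rely on. The analysis is not at stake.

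**Working it through.** No arithmetic applies and the plan gives no figure to reproduce. The check sets every statement about grades or stopping side by side.

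**1. Where grades appear.** They appear in three places: the cessation criteria, the severity table, and the table of reporting periods. Only the cessation criteria attach a stop to a grade. The reporting table groups grades 1 to 3 and gives grades 4 and 5 their own columns. Both tables therefore use grades as distinct labels, and neither carries the grade 3 rule upward.

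**2. Whether a symbol was lost.** This is unlikely. The same Methods section shows the MoCA-J limit of 26 with its greater-or-equal sign intact, and the exclusion criteria express the creatinine clearance limit as below 15 mL/min. The protocol writes thresholds out elsewhere, and the cessation sentence is complete.

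**3. What the protocol provides for a grade 4 event.**

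| Provision | Section | Automatic stop? |
| --- | --- | --- |
| Grade 3 criterion | Methods, cessation criteria | Not triggered if read literally |
| Stop after any adverse event, at the participant's request | Methods, cessation criteria | No, depends on the request |
| Stop for strong side effects | Burdens and foreseeable risks | No, permissive |
| Duty to deal with critical events and report them to the principal investigator | Obtaining information | No, mandatory management without a stated stop |
| Duty to respond and find the cause: "Investigators etc. must investigate their cause with extreme care of the participant" | Response to the adverse event / incident | No, mandatory management without a stated stop |
| First report "report: within 72h", second within 7 days | Table of reporting periods | No, reporting only |
| Action directed by the head of the institute; reports to the head | Report to joint research institution; What and how to report | No, case by case |

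No row supplies an automatic stop for grade 4.

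**4. Who stops.** The second cessation sentence uses the same phrase about the study being terminated for one person's refusal. One participant's refusal would not sensibly end the trial, so the phrase most likely means that person's participation. The wording is not uniform, though: the section on foreseeable risks speaks of participation when it means the individual.

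**5. Which grades are uncovered under each reading.**
- Participant level: grade 4 is literally uncovered. Grade 5 needs no rule, because there is no participation left to stop.
- Whole trial: grades 4 and 5 are both literally uncovered.

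**6. Why adding only the words for higher grades is not enough.** The subject of the sentence would still be the study, and the adverse event definition ignores causality. A literal reader could still take one unrelated event to end the trial. The corrected sentence has to name the participant.

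**The case against.** The strongest answer is that this is a copy-edit. Severity scales are ordered, and any reasonable investigator would take a stop at grade 3 to include grade 4. The English is rough throughout, so close parsing of one phrase may give it more weight than it can bear. The participants are healthy adults taking marketed supplements, and the section on foreseeable risks says no critical event has been reported, so on the protocol's own account a grade 4 event is unlikely. The duties to deal with critical events, to respond and to find the cause are mandatory.

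Most of this stands, and it keeps the point minor. It does not remove the point. A mandatory safety rule should not need its reader to supply the missing words, and none of the other duties is a stop.

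Two stronger readings are tempting, and the documents support neither:
- A reader might infer that the protocol leaves life-threatening events unmanaged. It does not: management is compulsory and reports are due within 72 hours and 7 days. Only the automatic stop is missing.
- A reader might infer that one grade 3 event among the 159 planned participants, related or not, would end the trial. The wording does not exclude this, but the parallel sentence on a participant's refusal makes it the less likely meaning. It is a reason to clarify the text and should not be reported as the plan's rule.

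**Conclusion.** The error is real and minor. As written, the only grade-based cessation criterion omits grade 4, and grade 5 as well if it is read at trial level. It also fails to say whether a participant or the whole trial stops. The practical gap is small, because the intent is almost certainly a participant-level threshold and few investigators would continue the product after a life-threatening event. No endpoint, estimate or sample size changes.

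That the omission exists rests on the text alone. That its effect is small rests on two judgements: that grade 3 was meant as a threshold, and that the phrase about terminating the study means the individual's participation, as the adjacent sentence suggests.

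**What to change.** Replace the first cessation sentence in Methods with: *A participant's participation will be terminated if that participant has any adverse event of grade 3 or higher (CTCAE v4.0-JCOG).* If a whole-trial stop is also wanted, state it in a separate sentence with its own trigger.

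The cost is one sentence, with no added participants, visits or data. If this is what was always meant, the memorandum described under Modification of the study protocol, which exists to settle literal interpretation, may be enough. Otherwise a protocol change is needed.

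Stopping only the product while keeping the 24-week assessments may be worth considering, but it is a separate change in how participants are handled. It would need a protocol change and could not be made by memorandum.

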# Study period

June 2021（post ethical approval）~ December 2022

# Items and methods of evaluation

# Primary endpoint

　To determine the efficacy of GBE/MST in the impact of cognitive function, data of GBE/MST will compare with that of GBE alone and placebo in healthy adults by the Wechsler Memory Scale-Revised (WMS-R) after 24 weeks.

# Secondary endpoint

1．Cognitive assessment

　a) MoCA-J …Screening of cognitive function

b) Trail Making Test-A, B　　…Screening of attention

c) Stroop test　　…Screening of frontal function

d) Tapping Span test　　…Screening of visual memory

　e) Digit Span test　　…Screening of verval memory

2．Brain MRI examination

The study also aims to evaluate the alterations in the default mode network (DMN) after 24 weeks of GBE/MST administration and compare them with the baseline data.

3．Physical assessment

　a)　 hight, body weight

　b)　 hand grip power、2 Step Test、Functional Reach Test

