# Sample size and rationale

# Sample size

Estimated sample number: 159（Control 53, GBE 53, GBE/MST 53）

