# Statistical analysis

# Statistical methods

(1) Analysis of cognitive function

The average of total WMS-R score at the endpoint will be compared among the GBE/MST, GBE, and placebo groups using one-way analysis of variance (ANOVA) and Tukey's test. The difference between the total score at baseline and at the endpoint will be compared among the three groups using multivariate ANOVA (MANOVA).

(2) Analysis of brain morphology

Total cerebral cortical volume will be calculated from the T1-weighted structural images using the SPM12 software. The average alteration in total volume from baseline to the endpoint will be compared among the three groups. Using the CONN toolbox (https://web.conn-toolbox.org/) implemented in MATLAB, functional connectivity (FC) between two regions of interest (ROIs) within the DMN will be analyzed by means of ROI-to-ROI analysis.

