# Methos and period of the study

# Study design

1. Study design
   1. **Control**

Placebo

- 1. **Randomization**

Double-blind

- 1. **Comparison**

Randamized placebo-controlled

1. **Rationale of the study design**

The primary aim of this study is to determine the efficacy of GBE/MST in the impact of cognitive function when compared with that of GBE alone and placebo in healthy adults using neuropsychological assessments. The study also aims to evaluate the alterations in the default mode network (DMN) after 24 weeks of GBE/MST administration and compare them with the baseline data.

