Standard blood and urine tests will be performed to check for health status. Body measurements, grasping power of both the hands, two-step test, and functional reach test will be performed at baseline and at the endpoint (24 weeks).

Cognitive tests will be completed by the participants at baseline and at the endpoint. The WMS-R and its lower domains will be used to measure total memory function and assess individual function (digit span indicates verbal memory and the tapping span indicates visual memory). Stroop Color and Word Test and Trail Making Test will be employed to assess executive functions such as restraint-related functions and sustained attention, respectively.

Magnetic resonance imaging (MRI: Achieva Intera 3T, Philips Healthcare, Quasar Dual, The Netherlands) will be performed at baseline and at the endpoint. T1 weighted magnetization-prepared rapid acquisition gradient echo (MPRAGE) structural images (matrix: 240 × 240, repetition time: 8.70 ms, echo time: 3.1 ms, flip angle: 8°, field of view: 256 × 256 × 180 mm, 162 slices, voxel size: 0.7 × 0.7 × 0.7 mm, and scan duration: 5 min 15 s) will be acquired to collect 3D structural datasets. Resting state functional MRI (rs-fMRI: T2*-weighted gradient-echo planar imaging, matrix: 64× 64, repetition time: 3000 ms, echo time: 30 ms, flip angle: 90°, field of view: 220 × 220 ×218 mm, 34 slices, voxel size: 3.44 × 3.44 × 3.40 mm and 197 volumes with 5 min superimposition) with closed eyes will be performed to analyze the DMN.

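### The default-mode-network endpoint is worded as GBE/MST against its own baseline, with no comparison to placebo or GBE alone

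*Protocol*

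**What the plan says.** The Protocol words the DMN aim the same way in two places. Under Rationale of the study design: "The study also aims to evaluate the alterations in the default mode network (DMN) after 24 weeks of GBE/MST administration", with the baseline data as the only comparator. Under Secondary endpoint, item 2 (Brain MRI examination), the alterations are those "after 24 weeks of GBE/MST administration and compare them with the baseline data".

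The cognitive aim, one sentence earlier in the design rationale, is to be judged "when compared with that of GBE alone and placebo in healthy adults using neuropsychological assessments". The Primary endpoint section also names both comparators.

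Statistical methods, item (2), covers two imaging measures. For total cortical volume: "The average alteration in total volume from baseline to the endpoint will be compared among the three groups". For the DMN: "functional connectivity (FC) between two regions of interest (ROIs) within the DMN will be analyzed by means of ROI-to-ROI analysis". The second statement names a connectivity measure and gives no contrast between arms.

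The schedule under Methods reads "Magnetic resonance imaging (MRI: Achieva Intera 3T, Philips Healthcare, Quasar Dual, The Netherlands) will be performed at baseline and at the endpoint", with no limit to one arm. The Sample size section plans 53 participants in each of the three arms.

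**The concern.** The endpoint names its own comparator, and that comparator is baseline. A change over 24 weeks in a single arm is the sum of any product effect and whatever else shifts measured connectivity over that time: scanner drift, greater ease in the scanner at the second visit, time of year. One arm alone cannot separate these.

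The abstract presents resting-state fMRI as the biological assessment that accompanies the neuropsychological tests. A significant before-after change in GBE/MST would therefore tend to be read as biological support for a cognitive effect, although the comparison behind it would be uncontrolled in a trial that randomises to two control arms.

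**Working it through.** **Step 1. The contrasts side by side.**

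| Outcome | Where defined | Comparator stated |
|---|---|---|
| WMS-R | Primary endpoint; Statistical methods (1) | GBE alone and placebo |
| Total cortical volume | Statistical methods (2) | Change compared among three groups |
| DMN connectivity | Rationale of the study design; Secondary endpoint | Baseline, GBE/MST only |
| DMN connectivity | Statistical methods (2) | None stated |

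The only DMN contrast the Protocol states is before versus after in GBE/MST.

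**Step 2. What each contrast estimates.** Let τ be the product effect on change in connectivity and δ the non-product change, common to all arms.
- Within GBE/MST: expected change = τ + δ.
- GBE/MST minus placebo: (τ + δ) − δ = τ.

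With τ = 0, the first contrast still tests δ; the second tests zero.

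**Step 3. Size, as an illustration.** The Protocol gives no figure and names no test for the DMN contrast, so there is nothing to reproduce. Inputs:
- n = 44, the per-group figure in the sample size rationale (derived there for WMS-R), and n = 53, the arm size with no dropout.
- Paired t-test at two-sided 0.05: assumed. The Protocol states α = 0.05 for WMS-R.
- Drift g = δ / SD of the change score, from 0 to 0.5: assumed, not in the documents.
- No product effect.

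Formula: rejection rate = P(T > c) + P(T < −c), where T is noncentral t with n − 1 degrees of freedom and noncentrality λ = g√n, and c is the 97.5% point of central t (2.017 for 43 df, 2.007 for 52 df). √44 = 6.633 and √53 = 7.280.

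| Drift g | λ, n = 44 | Rate, n = 44 | λ, n = 53 | Rate, n = 53 |
|---|---|---|---|---|
| 0 | 0 | 5.0% | 0 | 5.0% |
| 0.1 | 0.663 | 9.9% | 0.728 | 11.0% |
| 0.2 | 1.327 | 25.4% | 1.456 | 29.8% |
| 0.3 | 1.990 | 49.4% | 2.184 | 57.3% |
| 0.4 | 2.653 | 73.7% | 2.912 | 81.5% |
| 0.5 | 3.317 | 90.0% | 3.640 | 94.7% |

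**Step 4. The between-arm test under the same drift.** In 20,000 simulated trials with 44 per arm, a two-sample t-test on change rejected in 4.8%, 4.9% and 5.0% at g = 0, 0.2 and 0.4. A three-group ANOVA rejected in 4.8%, 4.8% and 5.1%.

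**Step 5. Limit of the 5%.** It holds per contrast. Two unadjusted contrasts, against placebo and against GBE, can together reach at most 2 × 5% = 10% for one ROI pair, and more if several pairs are tested. The between-arm contrast removes drift but not multiplicity.

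**The case against.** The strongest reply is that the wording in the design rationale and the Secondary endpoint section says only what is measured, namely alteration from baseline, and that the comparison is meant to follow the randomised, placebo-controlled design. The cortical volume sentence directly before the DMN sentence does compare three groups. The second-level contrast for a secondary imaging measure is also often left to an SAP, which may exist here but is not shown; the Protocol gives no contrast for its other secondary tests either.

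Part of this stands. Silence in Statistical methods is not an error in itself, and the point does not rest on it. It rests on the two places where a comparator is named and is baseline. An SAP that followed that wording would run a one-arm test; one that compared arms would depart from the endpoint as worded.

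A reader might infer more than the documents support:
- **That the control scans will be discarded.** No section says so. Statistical methods leaves the DMN contrast open; it does not state a within-arm test.
- **That all imaging is uncontrolled.** Cortical volume change is compared among the three groups.
- **That regression to the mean adds to the bias.** The eligibility criteria select on age, MoCA-J score and health, not on connectivity.
- **That the false-positive rate is known to be high.** The rates depend on assumed drift, and at zero drift the within-arm test also holds 5%.
- **That the efficacy conclusion is at risk.** The primary WMS-R comparison is between arms, and nowhere does the Protocol say that a causal claim will be drawn from DMN change alone.

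**Conclusion.** The concern holds for DMN connectivity, a secondary endpoint. The Protocol states a before-after contrast in GBE/MST, names neither control arm, and says nothing elsewhere that corrects this. That contrast cannot distinguish a product effect from a change shared by all arms.

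The structural conclusion needs no numerical assumption. The rates do: they assume a paired t-test, 44 analysed participants, no product effect and a drift size that the documents do not give. On that basis the chance of a spurious finding runs from 5% at zero drift through 10% at 0.1 SD to 90% at 0.5 SD, and is somewhat higher with 53. A between-arm test stays near 5% per contrast if the drift is common to the arms.

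**What to change.** Use one definition in Rationale of the study design, Secondary endpoint item 2 and Statistical methods item (2):
- The DMN endpoint is ROI-to-ROI connectivity at 24 weeks, compared among the three randomised arms and adjusted for baseline (or tested as group by time).
- The contrasts are GBE/MST versus placebo and GBE/MST versus GBE.
- Multiplicity is controlled over the ROI pairs and the two contrasts, by a rule named in advance.
- Within-arm change from baseline is reported descriptively only.

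The cost is a wording change and a group-level contrast in the connectivity analysis already planned. No scans are added, because MRI is scheduled at both visits without restriction by arm. The change also brings the DMN endpoint into line with the Protocol's between-arm treatment of cognition and cortical volume.
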